## Abstract

**Background:**

There is lack of ideal and comprehensive economic evaluations of various GDM strategies. The aim of this study is to the compare efficacy and cost-effectiveness of five different methods of screening for gestational diabetes mellitus (GDM).

**Methods:**

This study is a randomized community non-inferiority trial among 30,000 pregnant women in five different geographic regions of Iran, who were randomly assigned to one of the five GDM screening methods. All first trimester pregnant women, seeking prenatal care in governmental health care systems, who met our eligibility criteria were enrolled. The criteria suggested by the International-Association-of-Diabetes-in-Pregnancy-Study-Group, the most intensive approach, were used as reference. We used the non-inferiority approach to compare less intensive strategies to the reference one. Along with routine prenatal standard care, all participants were scheduled to have two phases of GDM screening in first and second-trimester of pregnancy, based on five different pre-specified protocols. The screening protocol included fasting plasma glucose in the first trimester and either a one step or a two-step screening method in the second trimester of pregnancy. Pregnant women were classified in three groups based on the results: diagnosed with preexisting pre-gestational overt diabetes; gestational diabetes and non-GDM women. Each group received packages for standard-care and all participants were followed till delivery; pregnancy outcomes, quality of life and cost of health care were recorded in detail using specific standardized questionnaires. Primary outcomes were defined as % birth-weight > 90th percentile and primary cesarean section. In addition, we assessed the direct health care direct and indirect costs.

**Results:**

This study will enable us to compare the cost effectiveness of different GDM screening protocols and intervention intensity (low versus high).

**Conclusion:**

Results which if needed, will also enable policy makers to optimize the national GMD strategy as a resource for enhancing GDM guidelines.

*Trial registration* Name of the registry: Iranian Registry of Clinical Trials. Trial registration number: IRCT138707081281N1. Date of registration: 2017-02-15. URL of trial registry record: https://www.irct.ir/trial/518

## Background

Gestational diabetes (GDM) defined as hyperglycaemia at any time during pregnancy at levels below those that occurring in overt diabetes [1]. It is one of the most common glycemic disorders during pregnancy with occurrence of 1–28% of all pregnancies [2–5], along with the increased rate of obesity and advanced maternal age is rising in prevalence [6]. It is well documented that GDM is associated with both short as well as long term higher rates of adverse feto-maternal and neonatal outcomes [7–11]. From an obstetrical perspective, evidence shows that treatment of GDM is effective in reducing the risk of many of the important adverse pregnancy outcomes [12–14].

Despite the globally accepted importance of screening for and treating GDM [13], screening strategies, testing methods and even diagnostic optimum glycemic thresholds for GDM remained much controversy for decades and no international consensus has been yet established [15]. In addition, the former screenings were mainly performed to prevent adverse maternal outcomes compared to neonatal complications. Considering this, use of different tests and criteria will impact the prevalence of women diagnosed with GDM [5], and could also impact poor pregnancy outcomes [16, 17]. There is also much controversy about milder forms of GDM. For which, the associations of mild GDM with adverse pregnancy outcomes are not completely understood; there is ongoing debate about the benefits of treating mild GDM and the impact on health care costs [18–21].

The Hyperglycemia and Adverse Pregnancy Outcomes (HAPO) study demonstrated that hyperglycemia at levels below those previous recommended thresholds for GDM were associated with adverse maternal and neonatal outcomes; hence, the International Association of Diabetes in Pregnancy Study Group (IADPSG) introduced new cutoffs for the 2-hour (2 h) oral glucose tolerance test (OGTT) in GDM screening and diagnosis [22]. Besides, at present, a 3-h 100 g diagnostic test is used predominantly in the United States and some other areas, whereas much of the world uses the 75 g, 2-h OGTT [5]. At present, there is little information regarding the sensitivity and specificity of these test, and hence the relative clinical effectiveness of the two-steps of the 1-h 50-g glucose challenge test (GCT) following 3-h 100 g oral glucose tolerance (OGTT) diagnostic test and the one-step OGTT approaches in the same population. However using the IADPSG criteria, two to threefold more women qualified for a diagnosis of GDM, potentially adding to the costs of care of the already large number of pregnant women [23–25].

With both increased prevalence and adopting lowering of the thresholds for diagnosis, the healthcare cost of GDM can be expected to rise proportionately. It follows that the debate as to whether or not a benefit exists in the treatment of GDM assumes even greater importance now than in the past. However, since in most countries, resources are inevitably scarce, healthcare interventions should be evaluated for their impact the on cost as well as effectivity on clinical outcomes [26]. Moreover, while not recognizing that GDM is associated with adverse pregnancy outcomes, over-diagnosis may lead to psychological stress, unnecessary treatments and impaired quality of life [27–29].

There is lack of ideal and comprehensive economic evaluations of various GDM strategies; the majority of existing cost-effective analyses are based on decision analysis modelling not real data, limited obtained from randomized clinical trials that documented controversial results [20, 30–38]. In addition most studies have been conducted in well-developed high-income countries which obviously have more developed healthcare systems than low and middle-income countries, where gestational diabetes has the highest prevalence. According to a WHO report, global and local decision-making regarding GDM strategies are challenging due to the lack of optimum economic evaluations of various GDM screening protocols, making it difficult to validated implement any national recommendations from a health economic perspective [31]. Since resources are unavoidably scarce, national health care interventions should be assessed for their impact on costs as well as on clinical outcomes; the most highly recommended practice is that economic evaluation should be an integral part of randomized clinical trials [39]; each population needs to adopt its community specific guidelines [40].

In this ongoing randomized community-field non-inferiority trial, we aimed to compare the cost-effectiveness of five different pre-defined GDM screening protocols, both one and two step, using different fasting plasma glucose thresholds to ascertain the optimum GDM screening protocol.

## Materials and methods

### Research questions and objectives

This study is being performed to provide real data collected from an unbiased population trial for assessment of the following hypothesis: (i) the prevalence of GDM when using the less intensive GDM screening strategies is not more than obtained using the IADPSG criteria. (ii) The pre-specified primary outcomes in less intensive GDM screening strategies are not worse than those obtained using IADPSG criteria. (iv) The cost of health care using less intensive GDM screening strategies is not higher than incurred using IADPSG criteria. (v) The numbers needed to treat (NNT) to prevent one primary outcome in less intensive strategies are the same as those obtained using IADPSG criteria.

The cost of prevention for one primary outcome in less intensive strategies is the same as that for IADPSG criteria.

According to our research hypothesis, primary outcomes hence are: percentage of birth weight > 90th percentile and primary cesarean section. Secondary outcomes are prevalence of neonatal hypoglycemia, birth weight < 10th percentile, neonatal admission to the intensive care unit, shoulder dystocia and birth trauma including fracture of clavicle and brachial plexus injury, intrauterine fetal death, preeclampsia and preterm labor, neonatal hyperbilirubinemia and hypocalcemia. In addition, the study will assess the direct health care costs including prenatal clinic visits, obstetrician visits, endocrinologist visits, dietician visits, blood glucose monitoring equipment, laboratory test cost, pharmacotherapy, additional fetal well-being assessments and hospitalization as well as indirect cost of productivity loss and charges to the family including traveling, food substitution, mother time off paid work, and partner time off work.

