### Randomization and allocation

Initially all provinces of Iran were categorized to five stratum based on their geographic location (North, East, West, South, and Center of Iran) and one province in each stratum were randomly selected; then, the list of the cities located in each province were provided. Since the socioeconomic status in the center of provinces may differ from other cities, in the second phase, all cities in each province were classified in two clusters of center of the province and other cities. At the end, four cities were randomly selected from the list of other cities in each province.

For allocation of protocols, in the cluster of the provincial centers, five different protocols were randomly allocated to each provincial center. Also, in the cluster of other cities, four other cities in each province were randomly allocated to the rest of the protocols (Fig. 1). Sample size for each city was estimated through probability proportional to size (PPS), defined by number of live births of the cities.

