### Intervention

Following the approval of this study, the study procedure was released as a guideline to all the selected cities. In this respect, workshops were conducted in each city to introduce the study protocol and train the caregivers and study staff accordingly. Dieticians, obstetricians, internal medics, laboratory technicians and endocrinologists in each province were invited to a scientific workshop to harmonize and coordinate the follow ups and treatment of GDM patients. Scientific teams with specialists and executive members conducted visits every 2 months. A telegram channel was developed for daily online communication of scientific members and executive members at both provincial and city levels to answer questions and solve any problems encountered.

Along with routine standard prenatal care, all pregnant women was screened for GDM based on the pre-specified protocol assigned to each city. In this respect, early screening of GDM was conducted in the first trimester of pregnancy, using fasting plasma glucose (FPG) from venous sample with the specific threshold based on each screening protocol; based on the results of those screening tests, pregnant women were classified in to three groups: (i) diagnosed with preexisting pre-gestational overt diabetes; (ii) gestational diabetes and (iii) non-GDM women. In addition, at 24–28 weeks of gestation, those not previously known to have diabetes (overt or gestational), were screened again for GDM based on pre-specified protocol criteria assigned to that city. All study participants were followed till delivery and pregnancy and neonatal outcomes and health cost were recorded in detail. Definitions of various protocols for screening are presented in Table 1.

**Table 1 Tab1:** Definitions of various protocols for screening of gestational diabetes mellitus

Protocol	First trimester	Second trimester		
	Diagnostic criteria for GDM	Method for GDM screening	Diagnostic threshold of test	Diagnostic criteria
A	92 mg/dL < FPG > 126 mg/dL	One step with 2-h 75 g OGTT	Fasting ≥ 92 mg/dL 1 h ≥ 180 mg/dL 2 h ≥ 153 mg/dL	GDM is defined as any of the given plasma glucose values are met or exceeded
B	100 mg/dL < FPG > 126 mg/dL	One step with 2-h 75 g OGTT	Fasting ≥ 92 mg/dL 1 h ≥ 180 mg/dL 2 h ≥ 153 mg/dL	GDM is defined as two or more of the given plasma glucose values are met or exceeded

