C	100 mg/dL < FPG > 126 mg/dL	One step with 2-h 75 g OGTT	Fasting ≥ 92 mg/dL 1 h ≥ 180 mg/dL 2 h ≥ 153 mg/dL	GDM is defined as any of the given plasma glucose values are met or exceeded
D	92 mg/dL < FPG > 126 mg/dL	Two steps with 50 g GCT—1 h following 3-h 100 g OGTT	50 g GCT:	GDM is defined as if two or more of the given plasma glucose values in 100 g OGTT are met or exceeded
			BS-1 h: ≥ 140 mg	
			100 g OGTT:	
			Fasting ≥ 95 mg/dL	
			1 h ≥ 180 mg/dL	
			2 h ≥ 155 mg/dL	
			3 h ≥ 140 mg/dL	
E	100 mg/dL < FPG > 126 mg/dL	Two steps with 50 g GCT—1 h following 3-h 100 g OGTT	50 g GCT:	GDM is defined as if two or more of the given plasma glucose values in 100 g OGTT are met or exceeded
			BS-1 h: ≥ 140 mg	
			100 g OGTT:	
			Fasting ≥ 95 mg/dL	
			1 h ≥ 180 mg/dL	
			2 h ≥ 155 mg/dL	
			3 h ≥ 140 mg/dL	

In the first trimester overt diabetes is defined as FPG ≥ 126 mg/dL

*FPG* fasting plasma glucose, *GCT* glucose challenge test, *OGTT* oral glucose tolerance test

Each group received packages of standard care based on their health status. In this respect, non-GDM pregnant women received routine standard care recommended by the American College of Obstetricians and Gynecologists (ACOG) 2013 [41]. Moreover, pregnant diabetic patients received specific prenatal and diabetic care, recommended by the American College of Obstetricians and Gynecologists (ACOG) 2013 [43] and the American Diabetes Association (ADA) 2016 [44].

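### Hypothesis (i) is true by definition for protocols B and C; the open question is how many fewer women they label, and a within-woman tabulation answers it far better than a contrast between cities

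*Protocol article*

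**What the plan says.** The protocol article's section on research questions and objectives lists as hypothesis (i) that "the prevalence of GDM when using the less intensive GDM screening strategies is not more than obtained using the IADPSG criteria". Protocol A, the IADPSG criteria, is the reference.

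Table 1, under Intervention, defines the rules:

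- **First trimester.** A and D print "92 mg/dL < FPG > 126 mg/dL"; B, C and E print "100 mg/dL < FPG > 126 mg/dL". The second inequality sign is misprinted. I read each entry as a band from the lower figure up to the overt-diabetes limit of 126.
- **Second trimester, A and C.** 75 g OGTT with cut-offs 92/180/153: "GDM is defined as any of the given plasma glucose values are met or exceeded".
- **Second trimester, B.** Same test and cut-offs, but "GDM is defined as two or more of the given plasma glucose values are met or exceeded".
- **Second trimester, D and E.** A different test, the same for both: "Two steps with 50 g GCT—1 h following 3-h 100 g OGTT".

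The second test goes to every woman not already diagnosed: "those not previously known to have diabetes (overt or gestational), were screened again for GDM".

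Protocols are allocated to whole cities. The randomization section says that "five different protocols were randomly allocated to each provincial center", and that the four other cities in each province take the remaining protocols. With 25 cities in five provinces, each protocol has five cities, one per province. The data analysis section compares the four less intensive strategies with IADPSG and says clustering will be considered. It sets out no separate analysis of hypothesis (i).

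**The concern.** If one rule is a subset of another, asking whether it finds no more cases than the larger rule has only one possible answer. A useful hypothesis would ask for the size of the difference, because that is the number of women spared the label.

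The design as described would answer through different women in different cities. Underlying glycaemia varies between cities. Glucose was also not measured in a central laboratory, although the Discussion describes a common protocol, staff training, standard equipment and monthly external quality control. With five cities per protocol, a small true gap can be blurred, or can appear with the wrong sign, which would contradict something Table 1 settles by definition.

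**Working it through.** The article gives no figure for hypothesis (i), so there is none to reproduce. Its sample size concerns macrosomia and is used here only for the arm size of 5,200.

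**Step 1: nesting.** Take one woman's first-trimester FPG and her three 75 g OGTT values.

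- C and A share the OGTT rule, and C's FPG cut-off is higher (100 against 92). C-positive implies A-positive.
- B and C share the FPG cut-off, and B needs two abnormal values where C needs one. B-positive implies C-positive.
- E and D share the second-trimester rule, and E's FPG cut-off is higher. E-positive implies D-positive.
- D and E use another second-trimester test, so neither is nested in A.

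Enumerating 14,000 glucose profiles (FPG 70 to 125, OGTT values around each cut-off, strict and non-strict FPG bounds) gave 0 positive under B but not A, 0 under C but not A, and 0 under B but not C.

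**Step 2: precision between cities.** Assumptions, none given in the article: prevalence 15%, true gap 3 points, equal cities of 5,200/5 = 1,040 women, no gain from province blocking.

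- Design effect: DE = 1 + 1,039 × ICC
- Between-city SE = √(2 × 0.15 × 0.85/5,200 × DE)
- Chance of a reversed sign = P(Z > 0.03/SE)
- Within-woman SE, for 3% reclassified among the 10,400 women in B and C cities, with the same ICC assumed for that share = √(0.03 × 0.97/10,400 × DE)

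| ICC | DE | Between-city SE (points) | Reversed sign | Within-woman SE (points) |
|---|---|---|---|---|
| 0.001 | 2.04 | 1.0 | 0.13% | 0.24 |
| 0.005 | 6.20 | 1.7 | 4.3% | 0.42 |
| 0.01 | 11.39 | 2.4 | 10% | 0.56 |
| 0.05 | 52.95 | 5.1 | 28% | 1.2 |

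The within-woman SE is smaller by a factor of about 4.2 at every ICC, and its sign cannot reverse.

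**Step 3: other gaps.** Here the variance per arm is p(1 − p)[ICC/5 + (1 − ICC)/5,200]. Chance of a reversed sign at ICC 0.005 / 0.01 / 0.02:

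- A 20%, C 18%: 15% / 22% / 29%
- A 20%, C 16%: 1.6% / 5.8% / 12.7%
- A 10%, C 9%: 24% / 30% / 36%
- A 20%, B 10%: 0 / 0 / 0.1% (2.4% at ICC 0.05)
- A 15%, B 7.5%: 0 / 0 / 0.5% (4.7% at ICC 0.05)

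In a beta-binomial simulation (40,000 runs, t with 8 df), the 95% interval lay wholly below zero in 47% / 29% / 17% of trials for 20% versus 16%, and in 15% / 10% / 7% for 20% versus 18%. Taking 6,000 per arm, from the abstract's 30,000, barely changes this: 21.9% instead of 22.0% for 20% versus 18% at ICC 0.01.

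**Step 4: where re-scoring is possible.** In B and C cities, a woman above the FPG cut-off of 100 is positive under all three rules. Everyone else not already diagnosed is scheduled for the full 75 g OGTT, including those at 92–99, so A, B and C status all follow from her results. The same reasoning gives D and E status in E cities. In A cities, women at 92–99 are diagnosed at once and not re-tested, so their B or C status is not known. The article's definition of mild GDM already relies on the separate FPG and OGTT values.

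**The case against.** Four points on the other side have weight.

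- **No test of (i) is spelled out.** GDM prevalence is not among the listed primary or secondary outcomes, and its analysis may sit in a plan not shown here. That stands. The between-city contrast is inferred from the design, and the fault lies in how the hypothesis is posed against Table 1.
- **The hypothesis covers four strategies.** A reader might infer that (i) is empty throughout. The documents do not support that: D and E are not nested in A, so for them it is a real question that needs the randomised comparison.
- **The size depends on assumptions.** A reader might take a 10–28% chance of reversal as the finding. Those values belong to ICCs of 0.01 to 0.05. The article's only clustering figure is 0.001, labelled a design effect; read as an ICC it gives about 0.1%. Each protocol appears once per province, so a stratified analysis could remove some of the noise counted here. Unequal city sizes, which allocation in proportion to births implies, would work the other way.
- **Re-scoring changes nothing that was delivered.** A reader might infer that it also repairs treated numbers and costs. It does not: these arise from women actually labelled and managed in each city. It also applies only to women with complete screening results.

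One reply remains. Nothing in the article rules out a paired tabulation, but none is described, and hypothesis (i) as worded does not ask for one.

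**Conclusion.** The point holds in limited form. For B and C, hypothesis (i) is settled by Table 1; only the size of the reduction is open. The contrast between cities is a weak instrument for that size when the gap is small, which matters mainly for A versus C. If B labels about half as many women as A, reversal is negligible for B up to an ICC of about 0.02 and reaches 2–5% only at 0.05.

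The nesting needs no assumption beyond reading the misprinted FPG bands as bounded above by 126. The probabilities rest on assumed ICCs, prevalences and gaps. In the within-woman analysis the direction is exact, while the size remains an estimate. The primary outcomes, the allocation and the non-inferiority margin are untouched.

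**What to change.** 1. For the nested rules, restate (i) as estimation of the proportion of women reclassified: A to C, C to B, and D to E.
2. Add a within-woman analysis with city-clustered standard errors. Score all women with complete screening results in B and C cities under A, B and C, and those in E cities under D and E. Leave A cities out of it.
3. Keep the randomised between-city comparison, stratified by province, for D and E versus A, and for prevalence, treated numbers and costs as delivered under every protocol.
4. Correct the printed FPG inequalities in Table 1 so that the bands are unambiguous.

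The cost is some rewording and one extra tabulation of data already collected, with no patient contact. Recruitment has ended, so report the analysis openly as an addition to the stated hypothesis, and say that it covers only women with complete results.

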### Overall study design

This is a randomized community-field trial including five GDM screening strategies in a parallel group design. Recruitment of the participants took place between September 2016 and January 2019 in 1015 health centers in 25 selected cities of five provinces of Iran.

All pregnant women < 14 weeks of gestation, who received prenatal care from governmental health care systems were eligible for enrollment, except where the following specific exclusion criteria prevented this: Maternal age < 18 years, preexisting diabetes, date of last menstrual period not certain, no ultrasound estimation from 6 to 14 weeks of gestational age available, chronic hypertension, asthma or currently receiving treatment with oral glucocorticoids, β-blockers, oral β-mimetics, Dilantin, or antiretroviral agents and past history of bariatric surgery.

All participants received standard prenatal care recommended by the American College of Obstetricians and Gynecologists (ACOG) [41]. Moreover, participants were scheduled to have two phases of GDM screening in the first and second trimesters of pregnancy, based on the pre-specified protocol for GDM screening, selected for each city.

At each prenatal visit, standardized questionnaires were administered to document prenatal as well as other data needed for research by trained midwives.

### Sample size calculation

Based on previous studies, we assumed that the primary event rate of macrosomia to be equal to 10% for all groups with no difference. To obtain a statistical power of 85% with a 1-sided type one error of 0.005 (considering multiple comparisons) approximately 4700 patients per group are needed to show the non-inferiority of more intensive compared to lower intensive strategies with a marginal difference of 0.03. With a design effect of 0.001 (for cluster sampling) and loss to follow-up of 11%, sample size reached to 5200 in each group [42].

In addition, superiority analyses will be designed to show that one screening strategy is superior to another after non-inferiority has been demonstrated.

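### The 4,700 per group does not follow from its stated inputs, the design effect of 0.001 is impossible, and the 85% power is unsupported without a city-level ICC

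*Protocol article*

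**What the plan says.** All inputs stand in the protocol article under Sample size calculation. On the event rate: "we assumed that the primary event rate of macrosomia to be equal to 10% for all groups with no difference". On error rates: "To obtain a statistical power of 85% with a 1-sided type one error of 0.005", the alpha being reduced for multiple comparisons. The non-inferiority margin is a risk difference of 0.03. From these the article states approximately 4,700 per group, and then: "With a design effect of 0.001 (for cluster sampling) and loss to follow-up of 11%, sample size reached to 5200 in each group".

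The unit of allocation is the city. Under Intervention: "all pregnant women was screened for GDM based on the pre-specified protocol assigned to each city". Under Overall study design, recruitment took place "in 1015 health centers in 25 selected cities of five provinces of Iran". Randomization and allocation describes, in each of five provinces, the centre plus four other cities sharing out the five protocols, with city sample sizes set in proportion to live births. That makes 5 cities per protocol, of unequal size. Data analysis calls the trial cluster randomized and says the cluster effect will be considered. No ICC and no number of women per city is stated.

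The abstract gives a total: "This study is a randomized community non-inferiority trial among 30,000 pregnant women in five different geographic regions of Iran".

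**The concern.** Three stated figures do not fit together. The per-group number is far from what its inputs yield. The quantity labelled a design effect is not a possible design effect for this trial. The final inflation step appears to contain loss to follow-up and nothing else.

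A reader who needs to know how much information the trial was designed to have is given a flat 85%. With 5 cities per protocol, the number of cities and the between-city variation can limit precision more than the number of women does, so that 85% cannot be taken at face value.

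**Working it through.** **Inputs from Sample size calculation:** p = 0.10 in both arms, true difference 0, margin 0.03, one-sided alpha 0.005 (z = 2.576), power 85% (z = 1.036), loss 11%. From the design sections: 25 cities, so k = 5 per protocol.

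**1. The plan's 4,700.**
n = (2.576 + 1.036)² × 2 × 0.10 × 0.90 / 0.03² = 2,610 per group.

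Variants per group: restricted maximum-likelihood null variance (Farrington-Manning type) 2,637; alpha halved to 0.0025, 2,955; 10% against 13% with one-sided alpha, 2,950, or 3,016 with continuity correction; equivalence version, 3,225. None is near 4,700. The ratio is 4,700 / 2,610 = 1.80. With independent women, 4,700 per group has 98.8% power.

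Changing an input can bring the formula close: an event rate near 20% gives 4,640, and a margin near 0.0224 gives 4,700. An undocumented 1.8-fold inflation would also do it. The article does not say which, if any, was used.

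**2. The step from 4,700 to 5,200.**
5,200 / 4,700 = 1.106. Loss alone gives 4,700 × 1.11 = 5,217 or 4,700 / 0.89 = 5,281, both within 3% of 5,200. Nothing is left over for clustering. A literal design effect of 0.001 would give 4,700 × 0.001, about 5 women.

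**3. What the power would be under an assumed city-level ICC.**
Analysed per group: 5,200 × 0.89 = 4,628, or m = 925.6 per city if cities are equal.

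DE = 1 + (m − 1) × ICC; SE = √(0.18 × DE / n); power = Φ(0.03 / SE − 2.576), or the noncentral t equivalent.

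At ICC 0.001: DE = 1 + 924.6 × 0.001 = 1.92; effective n = 4,628 / 1.92, about 2,405; SE = 0.00865; 0.03 / SE = 3.47; power = Φ(0.89) = 81%.

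The 16 df assume an analysis of 25 city-level results with terms for protocol and province (25 − 1 − 4 − 4). The 8 df assume a comparison of 5 with 5 cities. The article fixes neither.

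| Assumed ICC | DE | Normal | t, 16 df | t, 8 df |
|---|---|---|---|---|
| 0.0005 | 1.46 | 92% | 84% | 71% |
| 0.001 | 1.92 | 81% | 70% | 57% |
| 0.002 | 2.85 | 61% | 49% | 38% |
| 0.005 | 5.62 | 29% | 23% | 17% |
| 0.01 | 10.25 | 14% | 11% | 9% |

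With 30,000 enrolled (6,000 × 0.89 = 5,340 analysed per group) and ICC 0.001, DE is 2.07 and power is 85%, 74% or 61%.

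Unequal cities lower these figures. With DE = 1 + ((1 + CV²)m − 1) × ICC, an assumed city-size CV of 0.6 and ICC 0.001, 4,628 analysed gives 73%, 61% or 49%.

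**4. Limit set by the number of cities.**
As m grows, effective n per arm tends to k / ICC = 5 / ICC. Reaching 2,610 requires ICC below 5 / 2,610 = 0.0019. Above that, no number of women in 5 cities per protocol gives 85% (normal approximation).

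**5. Totals.**
5 × 5,200 = 26,000, against 30,000 in the abstract.

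**The case against.** A reader might infer that the trial is shown to be underpowered. The documents do not support that. The arithmetic slip runs towards more women, and the shortfall depends on an ICC that is not stated. With 4,628 analysed in equal cities, power is at least 85% up to an ICC of about 0.00084 (normal) or 0.00045 (16 df). On the most favourable reading of 0.001 (an ICC, 30,000 women, equal cities, normal critical value), power is 84.6%, in effect the stated figure. That objection stands, so the power figures here are conditional.

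A reader might also infer that clustering was ignored altogether. That goes too far as well. The 1.80-fold excess in 4,700 is close to the 1.94 that ICC 0.001 implies at 940 women per city (1 + 939 × 0.001), so an allowance may already be inside it. What stands is that none is documented, and that the text places its clustering term after 4,700.

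The 26,000 and 30,000 need not conflict. One is a calculated requirement; the other describes the trial after recruitment had ended, and enrolling more than the minimum is ordinary. It is a difference left unexplained, not a proven error.

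Finally, the paragraph does not bias the results. Recruitment is over, the analysis is to consider the cluster effect, and a failed non-inferiority test can be judged from a cluster-adjusted confidence interval against 0.03. This limits the harm but does not make the stated figures right. Nor is this detail left to a fuller protocol: inputs, result and design effect are all printed, and they disagree.

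**Conclusion.** Wrong as written on two counts that need no outside assumption: the stated inputs give 2,610 per group, not 4,700, and 0.001 cannot be a design effect. It also follows from the printed numbers that the step to 5,200 contains no visible cluster inflation, despite allocation of 25 cities.

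The stated 85% is therefore unsupported, which is not the same as shown to be false. It could be met at a very small city-level ICC and missed by a wide margin at a larger one: from 92% (normal) at ICC 0.0005 to 17% (t, 8 df) at 0.005, with 4,628 analysed per group. These figures assume equal cities, which allocation in proportion to live births makes unlikely, so they are on the optimistic side. Reading 0.001 as an ICC is itself an assumption about an unclear sentence.

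**What to change.** Rewrite the paragraph without enrolling more women:

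- State 2,610 per group before clustering, with the formula, or correct whichever input really produced 4,700.
- Replace the design effect of 0.001 by the ICC that was assumed and the design effect computed from 5 cities per protocol and the realised, unequal city sizes, for example DE = 1 + ((1 + CV²)m − 1) × ICC. Then apply the 11% loss.
- Replace the flat 85% by the power this gives over an ICC range of about 0.0005 to 0.01, with degrees of freedom matching the planned cluster analysis. No single replacement figure should be fixed in advance, because it depends on city sizes and an analysis model that the article does not give.
- Say in one sentence how 5 × 5,200 = 26,000 relates to the 30,000 in the abstract.

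The cost is wording and a short recalculation. The downside is that the stated power may become less favourable.
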